## 4.2 Toxicities and Dosing Delays/Dose Modifications

Any subject who receives treatment on this protocol will be evaluable for toxicity. Each patient will be assessed for the development of toxicity according to the Time and Events table in Section 5.4. Toxicity will be assessed according to the NCI Common Toxicity Criteria for Adverse Events (CTCAE), version 5.0. Dose adjustments should be made according to the system showing the greatest degree of toxicity.

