## 5.5 Removal of Subjects from Study

Subjects can be taken off the study treatment and/or study at any time at their own request, or they may be withdrawn at the discretion of the investigator for safety, behavioral or administrative reasons. The reason(s) for discontinuation will be documented and may include:

- 5.5.1 Subject voluntarily withdraws from treatment (follow-up permitted);
- 5.5.2 Subject withdraws consent (termination of treatment and follow-up);
- 5.5.3 Subject is unable to comply with protocol requirements;
- 5.5.4 Subject demonstrates disease progression (unless continued treatment with study drug/treatment is deemed appropriate at the discretion of the investigator);
- 5.5.5 Subject experiences toxicity that makes continuation in the protocol unsafe;
- 5.5.6 Treating physician determines continuation on the study would not be in the subject's best interest;
- 5.5.7 Subject becomes pregnant (pregnancy to be reported along same timelines as a serious adverse event);
- 5.5.8 Development of second malignancy (except for basal cell carcinoma or squamous cell carcinoma of the skin) that requires treatment, which would interfere with this study;
- 5.5.9 Lost to follow-up. If a research subject cannot be located to document survival after a period of 2 years, the subject may be considered "lost to follow-up." All attempts to contact the subject during the two years must be documented

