## 6.0 MEASUREMENT OF EFFECT

### 6.1 Antitumor Effect - Solid Tumors

#### 6.1.1 Definitions

Evaluable for toxicity. All subjects will be evaluable for toxicity from the time of their first treatment with study therapy.

Evaluable for objective response. Only those subjects who have measurable disease present at baseline, have received radiation, and have had their disease re-evaluated will be considered evaluable for response. These subjects will have their response classified according to the definitions stated below. (Note: Subjects who exhibit objective disease progression prior to the end of cycle 1 will also be considered evaluable.)

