### **6.3 Safety/tolerability**

Analyses will be performed for all subjects having received at least one fraction of radiation therapy. The study will use the CTCAE version 5.0 for reporting of adverse events.

[https://ctep.cancer.gov/protocolDevelopment/electronic\\_applications/ctc.htm](https://ctep.cancer.gov/protocolDevelopment/electronic_applications/ctc.htm)

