**7.2.1 Definitions**

An adverse event is defined as any untoward or unfavorable medical occurrence in a human research study participant, including any abnormal sign (for example, abnormal physical exam, imaging finding or clinically significant laboratory finding), symptom, clinical event, or disease, temporally associated with the subject's participation in the research, whether or not it is considered related to the subject's participation in the research.

Adverse events encompass clinical, physical and psychological harms. Adverse events occur most commonly in the context of biomedical research, although on occasion, they can occur in the context of social and behavioral research. Adverse events may be expected or unexpected.

Acute Adverse Events

Adverse events occurring in the time period from the delivery of radiation, through 90 days post treatment will be considered acute adverse events. *Adverse events will only be captured from medical oncology, radiation oncology, and surgical oncology clinic notes.*

***A dose- limiting toxicity (DLT) is a grade 3 toxicity deemed definitely related to treatment in the following categories: skin, rib bone (fracture), pulmonary (radiation pneumonitis), or neurological (intercostal or brachial plexus nerves) or any grade 4 or 5 toxicity deemed definitely attributed to the therapy.***

The following acute (<90 days) and late (>90 days – 36 months) toxicities definitely related to protocol treatment, as defined in CTCAE v5.0 will be reported

Grade 4 or higher toxicity in the below categories:

- Rib fracture
- Skin
- Radiation pneumonitis
- Neurologic
- Fat necrosis

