#### Late Adverse Events

Adverse events occurring in the time period from the end of acute monitoring (90 days), to 36 months/3 years post treatment, will be defined as late adverse events. After the 90 day acute period, we will only follow for grade 2 or higher toxicity: skin, rib/bone, bone (fracture), pulmonary (radiation pneumonitis), or neurological (intercostal or brachial plexus nerves) or any grade 4 or 5 toxicity deemed definitely attributed to the therapy. ***Adverse events will only be captured from medical oncology, radiation oncology, and surgical oncology clinic notes.***

***A dose- limiting toxicity (DLT) is a grade 3 toxicity deemed definitely related to treatment in the following categories: skin, rib bone (fracture), pulmonary (radiation pneumonitis), or neurological (intercostal or brachial plexus nerves) or any grade 4 or 5 toxicity deemed definitely attributed to the therapy.***

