#### Secondary Endpoints

Secondary endpoints for the phase I portion of this study include cosmetic outcome as evaluated by patient and physician. In addition, the following endpoints will be evaluated as secondary endpoints:

- Local Control
- Acute Toxicity (90 Days)
- Late Toxicity (24 months)
- Rates of Surgical Morbidity
- Pathologic Complete Response Rates
- Patient and Physician Cosmesis Outcomes
- Distant Disease-Free Survival

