### **10.3 Data Analyses**

#### Data Analysis Plans

Interim Reports: Interim reports will be prepared every twelve months from time of enrollment of first patient until enrollment is complete. In general, the interim reports will contain information about patient accrual rate with projected completion dates of the trial, status of QA review and compliance rate of treatment per protocol, and the frequencies and severity of toxicity.

The dose-limiting toxicity (DLT) and the maximum tolerable dosage (MTD) will be determined based on this Phase I design. The assessment of safety will be mainly based on the frequency of adverse events. The incidence of AEs together with the 95% confidence interval will be reported. The overall complete response rate and corresponding 95% confidence interval will be presented. Various survival rates such as local control, recurrence free survival, and distant disease-free interval will be computed using Kaplan-Meier curves along with the 95% confidence interval. Exact binomial method will be used to calculate the response rate, toxicity and the corresponding 95% confidence interval.

- Kaplan-Meier method will used to estimate the distant disease-free interval.

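### Late toxicity has a 24-month endpoint and a 36-month definition that are not reconciled, and the exact binomial over all treated patients understates it when follow-up is incomplete

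*Protocol*

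**What the plan says.** **Window.** The secondary objective (Protocol 2.2.3) and the secondary endpoint (10.1) are both worded "Late Toxicity (24 months" (closing bracket omitted). In 7.2.1, events from the end of the 90-day acute period "to 36 months/3 years post treatment, will be defined as late adverse events". The reporting list in the same section uses the longer window too: "The following acute (<90 days) and late (>90 days – 36 months) toxicities definitely related to protocol treatment". Toxicity visits are scheduled at both 24 and 36 months (4.5, 5.4).

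**Estimator.** Section 10.3 states: "Exact binomial method will be used to calculate the response rate, toxicity and the corresponding 95% confidence interval". It does not distinguish 90-day toxicity from late toxicity. The same section uses Kaplan-Meier for local control, recurrence-free survival and distant disease-free interval.

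**Denominator.** Section 4.2: "Any subject who receives treatment on this protocol will be evaluable for toxicity". Section 6.1.1: "All subjects will be evaluable for toxicity from the time of their first treatment with study therapy". Section 6.3, on safety: "Analyses will be performed for all subjects having received at least one fraction of radiation therapy". None of the three requires a minimum follow-up. The only follow-up requirement for toxicity is the 90 days that governs DLT assessment and escalation (10.1).

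**Incomplete follow-up.** Section 5.5 foresees withdrawal of consent, which ends follow-up, and loss to follow-up. Section 10.3 also plans interim reports every twelve months until enrolment is complete, with the frequency and severity of toxicity.

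**The concern.** There are two linked difficulties.

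First, the time point is not settled. A toxicity at month 30 is a late adverse event under 7.2.1 but falls outside the endpoint in 2.2.3 and 10.1. Two analysts could report different late-toxicity rates from the same data and each cite the protocol.

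Second, a binomial proportion has no censoring. If all treated patients are in the denominator and only observed events are in the numerator, a patient who leaves at month 6 contributes the same as one seen free of toxicity at month 24. Section 7.2.1 takes adverse events only from oncology clinic notes, so a patient who stops attending generates no late events but stays in the denominator. Annual reports during accrual have the same difficulty, because recently treated patients cannot yet have 24 months of follow-up.

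At stake is a named secondary safety endpoint of a trial that gives one large fraction. The error, where it occurs, goes in the reassuring direction.

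**Working it through.** **What can be reproduced.** The protocol states no late-toxicity rate, precision or loss figure. Its maximum size does reproduce: 4 dose levels × 15 = 60 (10.2). The rest is conditional on assumptions.

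**Assumptions (not in the protocol).** True late-toxicity rate 20% at 24 months; constant hazard from month 3; constant loss hazard from month 0, with loss of 0%, 10% or 20% by month 24; uniform accrual. The 5-year study duration in the Study Summary is used as a data cut for illustration only.

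**Step 1: the window.** The late period lasts 24 − 3 = 21 months or 36 − 3 = 33 months, a ratio of 33/21 = 1.57. At a constant hazard, 20% at 24 months corresponds to 1 − 0.8^(33/21) = 29.6% at 36 months. For assumed 24-month rates of 10% and 30%, the 36-month figures are 15.3% and 42.9%.

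**Step 2: the denominator, every patient potentially followed to month 24.** With 60 months from first accrual to the cut, this means accrual over 36 months or less. Event hazard h = −ln(0.8)/21 = 0.01063 per month; loss hazard c = −ln(1 − d)/24, where d is the proportion lost by month 24.

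Expected crude rate = e^(−3c) × h/(h + c) × [1 − e^(−21(h + c))]

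| Loss by month 24 | c per month | Calculation | Crude rate | Relative to 20% |
|---|---|---|---|---|
| 0% | 0 | 1 × 1 × 0.2000 | 20.0% | 0 |
| 10% | 0.00439 | 0.9869 × 0.7076 × 0.2705 | 18.9% | −6% |
| 20% | 0.00930 | 0.9725 × 0.5333 × 0.3419 | 17.7% | −11% |

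If loss starts at month 3 instead, the crude rates are 19.0% and 18.0% for 10% and 20% loss. In simulation under that variant, 1 minus Kaplan-Meier averaged 19.9% to 20.1% for 10% to 30% loss, with 15 or 60 patients.

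**Step 3: administrative cut-off.** With accrual over 48 months and a cut at month 60, three quarters of patients have at least 24 months of potential follow-up. The last quarter have 12 to 24 months, and their average event probability without loss is 1 − (e^(−9h) − e^(−21h))/(12h) = 1 − (0.9088 − 0.8)/0.1275 = 14.7%. Overall: 0.75 × 20% + 0.25 × 14.7% = 18.7%. With 20% loss, averaging the Step 2 expression over the follow-up distribution gives 16.6%.

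**Step 4: size beside sampling error.** In one full cohort, 3 of 15 is 20% with an exact 95% interval of 4.3% to 48.1%. If only 12 of the 15 had an event or complete follow-up, 3 of 12 is 25% (5.5% to 57.2%). A shift of about 1 to 3 percentage points is small against either interval.

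**The case against.** **The denominator for a late rate is not spelled out.** No sentence says that an unobserved patient is counted as free of toxicity, and an exact binomial could also be applied to patients with an event or complete follow-up. That is fair: the treatment of such patients is inferred. But three sections place all treated patients in the toxicity or safety population, none adds a follow-up condition, and 10.3 names a method without censoring. The understatement is what results from following the text as it stands. A statistical analysis plan may settle it; this protocol points the other way.

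**The two windows need not conflict.** A 24-month endpoint inside a 36-month collection period is a natural reading, and there are visits at both times. It is probably what was meant, but nothing says so.

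**The direction depends on the window.** If events to month 36 are counted and the result is set against the 24-month truth, the crude figure exceeds 20% under the same assumptions. That stands, and it is a reason to fix the window. Against the truth at the same time point, the crude rate is never too high in expectation.

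**Stronger readings that the documents do not support.** A reader might infer that the highest dose will look safer because its patients are treated last. That needs accrual long enough, and a data cut early enough, to truncate the last patients. No accrual period or analysis date is given, and 4.5 speaks of 5 years of follow-up. With accrual of 36 months or less and a month-60 cut there is no administrative effect at 24 months. A reader might also take the loss rule in 5.5.9 ("If a research subject cannot be located to document survival after a period of 2 years") as keeping lost patients in the analysis as event-free. It is an administrative status tied to survival, not an analysis rule. Finally, the list of Kaplan-Meier outcomes in 10.3 is given by way of example, so it does not show that toxicity alone was deliberately left out.

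**Conclusion.** The point holds in a limited form. The 24- and 36-month time points are both in force and their relation is not stated. The all-treated exact binomial, applied as written to late toxicity, understates the cumulative rate at whichever time point is chosen if any patients at risk are not followed to it. The direction is certain under incomplete follow-up, and the bias is zero under complete follow-up.

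The size is unknown, because the protocol gives no loss, accrual or late-toxicity figures. Under the assumptions shown it is about 1 to 3.5 percentage points on a true 20%. That is well inside the sampling uncertainty at 7 to 15 patients per level. Escalation, DLT and MTD decisions rest on 90-day data and are not affected. The change is worth making because it is cheap and the error favours an impression of safety, not because any trial decision is at risk.

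**What to change.** In 10.3, keep the exact binomial for 90-day acute toxicity and DLTs. For late toxicity, specify a time-to-event estimate by dose level: 1 minus Kaplan-Meier, or cumulative incidence if death is treated as competing. Time it from radiation and censor at the last toxicity assessment. Report it at 24 months as the secondary endpoint and also at 36 months, with 95% confidence intervals and numbers at risk. Use the same estimate wherever interim reports quote late toxicity.

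In 2.2.3, 7.2.1 and 10.1, state that 24 months is the endpoint within a 36-month collection period, or reconcile the two in another explicit way.

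The cost is protocol wording and one routine analysis of data already scheduled for collection. The reported rate may be slightly less favourable and its interval slightly wider.

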## **11.0 STUDY MANAGEMENT**

### **11.1 Conflict of Interest**

Any investigator who has a conflict of interest with this study (patent ownership, royalties, or financial gain greater than the minimum allowable by their institution, etc.) must have the conflict reviewed by the UTSW COI Committee and IRB according to UTSW Policy on Conflicts of Interest. All investigators will follow the University conflict of interest policy.

### **11.2 Institutional Review Board (IRB) Approval and Consent**

It is expected that the IRB of record will have the proper representation and function in accordance with federally mandated regulations. The IRB of record must approve the consent form and protocol.

In obtaining and documenting informed consent, the investigator should comply with the applicable regulatory requirement(s), and should adhere to Good Clinical Practice (GCP) and to ethical principles that have their origin in the Declaration of Helsinki.

Before recruitment and enrollment onto this study, the subject will be given a full explanation of the study and will be given the opportunity to review the consent form. Each consent form must include all the relevant elements currently required by the FDA Regulations and local or state regulations. Once this essential information has been provided to the subject and the investigator is assured that the subject understands the implications of participating in the study, the subject will be asked to give consent to participate in the study by signing an IRB-approved consent form.

Prior to a patient's participation in the trial, the written informed consent form should be signed and personally dated by the subject and by the person who conducted the informed consent discussion.

### **11.3 Registration/Randomization Procedures**

All subjects must be registered with the Radiation Oncology CRO before enrollment to study. Prior to registration, eligibility criteria must be confirmed with the Radiation Oncology CRO Study Coordinator.

New subjects will receive a number beginning with 001 upon study consent such that the first subject consented is numbered 001, the second subject consented receives the number 002, etc.

Upon confirmation of eligibility and enrollment as per the afore-mentioned instructions, the subject will be assigned a secondary number in the order of enrollment. For example, subject 001 will become 001-01 upon enrollment. If subject 002 screen fails, and subject 003 is the next subject enrolled, subject 003 will become 003-02 and so-on.

Each newly consented subject should be numbered using the schema provided above. Upon registration, the registrar will assign the additional registration/randomization code according to the numbering schema outlined above, which should then be entered as the patient study id in Velos upon updating the status to enrolled.

The numbering schema should clearly identify the site number; the sequential number of the subject consented as well as the status of the subjects enrolled so that the number of subjects consented versus the number of subjects actually enrolled may be easily identified.

## **11.4 Data Management and Monitoring/Auditing**

### **11.4.1 Data Management**

REDCap is the UTSW SCCC institutional choice for the electronic data capture of case report forms for SCCC Investigator Initiated Trials. REDCap will be used for electronic case report forms in accordance with Simmons Comprehensive Cancer Center requirements, as appropriate for the project.

### **11.4.2 Trial Monitoring**

Trial monitoring will be conducted no less than annually and refers to a regular interval review of trial related activity and documentation performed by the DOT, which includes but is not limited to accuracy of case report forms, protocol compliance, timeliness and accuracy of Velos entries and AE/SAE management and reporting. Documentation of trial monitoring will be maintained along with other protocol related documents and will be reviewed during internal audit.

### **11.4.3 Trial Audits**

Toxicity reviews will be performed annually from the day of the first patient enrollment, and dose escalation and/or de-escalation will be performed at the time of dose escalation and/or de-escalation on this study. The report will be stored in the digital regulatory repository.

The UTSW Simmons Comprehensive Cancer Center (SCCC) Data Safety Monitoring Committee (DSMC) is responsible for monitoring data quality and patient safety for all UTSW SCCC clinical trials. As part of that responsibility, the SCCC DSMC reviews all serious adverse events and UPIRSOs in real time as they are reported and reviews adverse events on a quarterly basis. The quality assurance activity for the Clinical Research Office provides for periodic auditing of clinical research documents to ensure data integrity and regulatory compliance. A copy of the DSMC plan is available upon request.

The SCCC DSMC meets quarterly and conducts annual comprehensive reviews of ongoing clinical trials, for which it serves as the DSMC of record. The Quality Assurance Coordinator (QAC) works as part of the DSMC to conduct regular audits based on the level of risk. Audit findings are reviewed at the next available DSMC meeting. In this way, frequency of DSMC monitoring is dependent upon the level of risk. Risk level is determined by the DSMC Chair and a number of factors such as the phase of the study; the type of investigational agent, device or intervention being studied; and monitoring required to ensure the safety of study subjects based on the associated risks of the study. Protocol-specific DSMC plans must be consistent with these principles.

## **11.5 Adherence to the Protocol**

Except for an emergency situation, in which proper care for the protection, safety, and well-being of the study subject requires alternative treatment, the study shall be conducted exactly as described in the approved protocol.

Any deviation from the protocol requirements, whether pre-approved or unexpected, are to be recorded/logged as a protocol deviation and reported per institutional policy.

- 11.5.1 Exceptions** (also called single-subject exceptions or single-subject waivers): include any departure from IRB-approved research that is *not due to an emergency* and is:
- intentional on part of the investigator; and/or
  - in the investigator's control; and/or
  - not intended as a systemic change (e.g., single-subject exceptions to eligibility [inclusion/exclusion] criteria)
- **Reporting requirement\***: Exceptions are non-emergency deviations that require **prospective** IRB approval before being implemented. Call the IRB if your request is urgent. If IRB approval is not obtained beforehand, this constitutes a major deviation. For eligibility waivers, studies which utilize the SCCC-DSMC as the DSMC of record must also obtain approval from the DSMC prior to submitting to IRB for approval.
- 11.5.2 Emergency Deviations**: include any departure from IRB-approved research that is necessary to:
- avoid immediate apparent harm, and/or
  - protect the life or physical well-being of subjects or others
- **Reporting requirement\***: Emergency deviations must be promptly reported to the IRB within 5 working days of occurrence.
- 11.5.3 Serious Noncompliance (formerly called major deviations or violations)**: include any departure from IRB-approved research that:
- increase risk of harm to subjects; and/or adversely affects the rights, safety, or welfare of subjects (any of which may also be an unanticipated problem); and/or
  - adversely affects the integrity of the data and research (i.e., substantially compromises the integrity, reliability, or validity of the research)
- **Reporting requirement\***: Serious noncompliance must be promptly reported to the IRB within 5 working days of discovery.
- 11.5.4 Continuing Noncompliance**: includes a pattern of repeated noncompliance (in one or more protocols simultaneously, or over a period of time) which continues **after** initial discovery, including inadequate efforts to take or implement corrective or preventive action within a reasonable time frame.
- **Reporting requirement\***: Continuing Noncompliance must be promptly reported to the IRB within 5 working days of discovery.
- 11.5.5 Noncompliance (that is neither serious nor continuing; formerly called minor deviations)** any departure from IRB-approved research that:
- Does not meet the definition of serious noncompliance or continuing noncompliance
- **Reporting requirement\***: Noncompliance that is neither serious nor continuing should be tracked and summarized at the next IRB continuing review, or the notice of study closure- whichever comes first.

\*Reporting Requirements reflect UTSW HRPP/IRB guidelines; participating sites should follow the reporting guidelines for their IRB of record.

